### Delivery of interventions

The interventions will be delivered by trained art and music therapists. Activities in each intervention is structured and planned for the whole study period.

### Art therapy

The AT activity was developed by the team in consultation with art therapists. It will have two components: creation of art pieces; and viewing and discussing art pieces with narration of thoughts and inner experiences. Studies have shown that visual art production interventions and cognitive art evaluation groups benefit the individual but in slightly different ways [27]. Hence, this study will include both activities and consider them as one intervention.

The guided viewing and making of visual images and talk therapy with an art therapist contributes to externalization of thoughts and feelings which may otherwise remain unexpressed. Each weekly session will begin with mindful relaxation to help the participants focus on the task ahead. They will be asked to draw anything they want or what they think is relevant to the topic for each session. They will then be asked to share about the picture they have created, feelings, and perspectives, first in pairs and then with the group where image appreciation activities will be used to help participants gain insights and discuss their feelings.

In addition, participants will visit both the National Art Gallery and the National University of Singapore Art Museum once a month in the first three months. They will view displayed artworks in guided sessions and will be invited to share their views and feelings about the artefacts. Each of the AT sessions will last 1 h (inclusive of 5 min of mindful relaxation and a 15-min break). From the fourth to ninth month, fortnightly AT sessions are provided with sessions at the study center alternating with sessions at the National Art Gallery or National University of Singapore Art Museum. Participants will visit the Art Gallery and Art Museum, first, because the art pieces cannot be removed from these places and brought to the research center; second, two sites are involved because neither one of the sites has sufficient docents to manage the number of visits alone. With two sites, each site will host the participants’ visit only once a month in the first three months and then in alternate months for the next six months. Participants will be taken to the Art Gallery and Museum by coach and will be accompanied by research staff during the 15-min journey.

#### Content of the art therapy intervention

Weekly sessions:Session 1: Art and expressionSession 2: FriendshipSession 3: Visit to the NUS Art MuseumSession 4: Visit to the National Art GallerySession 5: Emotions and feelingsSession 6: FamilySession 7: Visit to the NUS Art MuseumSession 8: Visit to the National Art GallerySession 9: HappinessSession 10: Hopes and wishesSession 11: Visit to the NUS Art MuseumSession 12: Visit to the National Art Gallery

Fortnightly sessions:Session 13: Art activitySession 14: Visit to the NUS Art MuseumSession 15: Art activitySession 16: Visit to the National Art GallerySession 17: Art activitySession 18: Visit to the NUS Art MuseumSession 19: Art activitySession 20: Visit to the National Art GallerySession 21: Art activitySession 22: Visit to the NUS Art MuseumSession 23: Art activitySession 24: Visit to the National Art Gallery

### Music reminiscence activity

Reminiscence therapy with music entails listening and discussing activities, events, and experiences related to the music. Sessions will be presented as music videos, with additional prompts in the form of photographs, to facilitate therapy. Participants who agree will be asked to bring 10–20 photographs and also choose songs or music for the videos. Reminiscence provokes shared feelings and boosts self-esteem while the group process provides validation for each member [28]. The structured activity was previously planned by the team and used effectively in the earlier naturalistic study [11]. Participants will meet weekly for the first three months and then fortnightly for six months. As in the AT intervention group, each session will begin with a 5-min mindful relaxation and the 1-h session will include a 15-min break.

#### Content of the music reminiscence activity

Weekly sessions:Session 1: Introduction and ice-breaking sessionSession 2: Family of originSession 3: House/Place I grew up inSession 4: ChildhoodSession 5: Childhood gamesSession 6: SchoolSession 7: My favorite teacher, subject, classmateSession 8: OccupationSession 9: Significant events/achievementsSession 10: FriendshipsSession 11: My best friendSession 12: Family/Marriage

Fortnightly sessions:Session 13: Parents/ChildrenSession 14; Hobbies, sports and gamesSession 15: Holidays and travelSession 16: My favorite place in SingaporeSession 17: Favorite foodSession 18: Memorable songsSession 19: FestivalsSession 20: Famous actors/singersSession 21: Recreational placesSession 22: Old moviesSession 23: Favorite parksSession 24: Termination; group discussion

### Control group

The control group will not receive any intervention but continue their life as usual.

### Study setting

Data collection will be done by trained nurses and research assistants blinded to the group assignment at a community research center used by the university, named the Training and Research Academy at Jurong Point (TaRA@JP).

### Measures

A questionnaire on demography will include a basic health screen (weight, height, BP, and PR at baseline and repeated [with the exception of height] at three and nine months). Functional assessment will be done using the Activities of Daily Living (ADL) questionnaire and the instrumental ADL (iADL).

Subjective cognitive impairment will be assessed using the Perceived Deficits Questionnaire (PDQ). It consists of 20 questions answered on a five-point Likert scale. Scores range from 0 to 80, with higher scores indicating severe impairment.

Cognitive assessments will be done with the following validated assessment scales:Mini-Mental State Examination (MMSE), a brief 30-point questionnaire, will be used to screen for cognitive impairment. Scores range from 0 to 30, with higher scores indicating less impairment;Clinical Dementia Rating (CDR) Scale is a five-point scale used to characterize six domains of cognitive and functional performance applicable to Alzheimer’s disease and other dementias: memory, orientation, judgment and problem-solving, community affairs, home and hobbies, and personal care;Neuropsychological tests:Rey Auditory Verbal Learning Test (RAVLT) evaluates declarative verbal learning and memory;Digit Span Task consists of a Digit Span Forward (DSF) and Digit Span Backward (DSB) and is used to assess attention and verbal working memory;Color Trails Test (CTT) 1 and 2 assess sustained attention and memory;Block Design, a subtest of the Wechsler Intelligence Tests, measures visual–spatial and organizational processing abilities and non-verbal problem-solving skills.

Psychological wellbeing assessment will be assessed with the:Geriatric Depression Scale (GDS): a 15-item “yes/no” questionnaire with higher total scores associated with higher risk of depression;Geriatric Anxiety Inventory (GAI): a 20-item “agree/disagree” questionnaire measuring dimensional anxiety, with higher total scores associated with anxiety symptoms.

Participants with high GDS score (≥5) and/or high GAI score (≥ 10) will be clinically assessed using the Structured Clinical Interview for DSM Disorder (SCID) to rule out major psychiatric disorders (e.g. generalized anxiety disorder or major depressive disorder).

#### Neuroimaging assessment of functional connectivity and structure of the brain

Functional magnetic resonance imaging (fMRI) will be employed to examine changes in functional connectivity. Images will be acquired on a 3 T Siemens scanner using a standard Siemens whole head coil. Twenty-eight axial slices (4-mm thick, 1-mm skip) parallel to the plane connecting the anterior and posterior commissures and covering the whole brain will be imaged using a T2*-weighted gradient echo spiral pulse sequence (repetition time/echo time = 2000/30 ms; flip angle = 80°; and interleave = 1). The field of view will be 200 × 200 mm^2^ and the matrix size 64 × 64, yielding an in-plane isotropic spatial resolution of 3.125 mm. An automated high-order shimming method based on spiral acquisitions will be used before acquiring fMRI scans. All participants will undergo the task-free fMRI scan after being instructed only to remain awake with their eyes closed.

White matter diffusion tractography imaging (DTI) will be utilized to identify anatomical connections between functionally correlated regions. Anatomic T1-weighted scans will be obtained on a 3 T Siemens scanner with the following parameters: repetition time = 2100 ms; flip angle = 12°; slice thickness = 1.5 mm; inversion time = 1100 ms; matrix = 192 × 256; field of view = 172.5 mm; echo time = 3.87 ms. The DTI will be acquired in one non-weighted and six diffusion-weighted non-collinear directions with an echo-planner sequence with diffusion weighting 9b value of 1000 smm^−1^. A dual spin echo will be used to minimize distortion due to eddy currents. Imaging parameters are: repetition time = 6100 ms; flip angle = 90°; field of view = 178 × 219; matrix = 104 × 128; voxel size = 1.71 × 1.71. × 4 mm; number of averages = 4; echo time = 92 ms.

The control group will do baseline questionnaires and investigations similar to participants in the two intervention arms. They will do the neuroimaging at baseline and three months as well as the other investigations, similar to those in the two intervention arms. The only difference is the control group will not have blood samples taken at three months.

The fMRI scanning will be task-free. It is non-invasive and does not involve any injection of tracer dyes.

Caregivers will be asked to complete the Zarit Burden Scale at baseline, three months, and nine months. This is optional and caregivers can choose not to complete this scale and this will have no impact on subject participation. Caregivers will be asked to complete a portion of the Clinical Dementia Rating at baseline (if they are present or available) (Fig. 2).

### Recruitment

Participants will be recruited from amongst elderly individuals living around TaRA@JP and known to the research center. Only participants who agreed to be contacted for future research and known to have early cognitive impairment will be contacted by phone and invited to participate in the current study.

Others who have heard about the study will be recruited if they meet inclusion criteria and reside within close proximity to the research site (TaRA@JP) for travel arrangements.

They will be informed of the study and provided with a copy of the invitation letter and participant information sheet – both English and Mandarin versions will be made available to them. They will be given time to read the document in a private area at TaRA@JP and given time to consider whether to agree to participate in the study.

Nurses will interpret orally for those who are illiterate and for those who do not understand English. A Short Consent Form (Mandarin) will be used for the participant’s signature (or thumb print) and an impartial witness will be present and sign the document as well. If a translator is involved in the consent taking, he/she will also sign the consent form.

### Outcomes

Primary outcome measures:Improvements in neuropsychological test scores at three months and nine months;Positive changes in cerebral functioning at three months.

Secondary outcome measures:Improvement in GDS and GAI scores at three months and nine months;Increase in telomere lengths at three months and nine months.

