## Methods/Design

### Aims of study

This pilot study aims to explore the feasibility of using AT and MRA to improve the cognition of community living elderly with MCI (Diagnostic and Statistical Manual-5: Mild Neurocognitive Disorder) [2].

The primary outcomes will be the structural cerebral changes that occur with the two interventions and the extent to which the therapies may reverse cognitive impairment and/or prevent further cognitive decline on neuropsychological tests of cognition. This will be based on participants’ pre-, three-month and nine-month neuropsychological test scores, compared with individuals in the control arm who do not participate in active interventions.

Secondary outcomes comprise changes in blood biomarkers, psychological wellbeing, and mood symptoms.

We hypothesize that participants in both active intervention arms will have (1) improved functional connectivity, (2) improved neuropsychological cognitive test scores, (3) increased telomere lengths, and (4) enhanced psychological wellbeing and reductions in anxiety and depressive symptoms compared with the control group.

No a priori hypotheses were developed as to whether AT or MRA is more effective as the comparison is exploratory.

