#### Nine months (study end)

Basic health screen (excluding height), functional assessment, neuropsychological tests, and blood investigations are repeated.

The time taken for the health screening, completion of the demographic data, main questionnaire, and blood sample collection will take about 1 h.

The neuropsychological tests will take about 1 h 45 min. The baseline visit to TaRA@JP will take about 3 h. Subsequent visits at three months and nine months will take 2 h.

The fMRI scans will be conducted at CIRC in NUS and the appointment will be on another day. The imaging sessions will take 1 h. However, the time within the scanner is about 45 min.

See Tables 1 and 2 for the visit schedules for the interventions and control groups, respectively.

**Table 1 Tab1:** Visit schedule for intervention arms

Pre-baseline/Baseline	Three months	Nine months (study end)
Informed consent process	Main questionnaire	Main questionnaire
Eligibility screening	Neuropsychological tests	Neuropsychological tests
Demographic data	MRI scan	Clinical Dementia Rating
Main questionnaire	Weight, vital Signs	Weight, vital signs
Neuropsychological tests	Blood sample collection	Blood sample collection
Clinical Dementia Rating		
MRI scan		
Basic health screen		
Blood sample collection

**Table 2 Tab2:** Visit schedule for controls

Pre-baseline/Baseline	Three months	Nine months (study end)
Informed consent process	Main questionnaire	Main questionnaire
Eligibility screening	Neuropsychological tests	Neuropsychological tests
Main questionnaire	MRI scan	Clinical Dementia Rating
Demographic data	Weight, vital signs	Weight, vital signs
Neuropsychological tests		Blood sample collection
Clinical Dementia Rating		
MRI scan		
Basic health screen		
Blood sample collection		

Blood samples (3 mL) will be collected at three time-points for those in the AT and MRA arms (baseline, three months, nine months) for telomere lengths. For the control group, it will be done twice, at baseline and at nine months.

Samples will be stored immediately in a mini-fridge (4 °C) at TaRA@JP and transported within 12 h of collection to the labs.

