### Statistical analyses

All efficacy analyses will be carried out on an intention-to-treat (ITT) basis. That is, all randomized participants will be included in the analysis and the intervention group of participants will be according to the randomization list planned prior to the intervention commencement.

The primary outcomes – neuropsychological test scores – at baseline, three months, and nine months will be modeled using the linear mixed model for repeated measurements. Differences in the estimated means of the changes at three and nine months from baseline between the intervention and control groups and their associated 90% and 95% confidence intervals will be calculated. Further, analysis may be performed to adjust the model for potential confounders, such as age, gender, and education level. Secondary outcomes (cerebral functioning, the GDS and GAI scores, and telomere lengths) will be analyzed similar to the primary outcomes.

Demographic and other baseline characteristics and reported adverse events and serious adverse events will be summarized using descriptive statistics.

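### The three-month telomere comparison with control cannot be estimated, because controls give no blood at three months; the nine-month comparison is unaffected

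*Protocol article*

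**What the plan says.** Four parts of the protocol article bear on this.

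- **Outcome.** Outcomes lists, among the secondary measures, "Increase in telomere lengths at three months and nine months".
- **Comparator.** Aims of study gives four hypotheses for the two active arms in one sentence. Longer telomeres are the third, and the sentence ends "enhanced psychological wellbeing and reductions in anxiety and depressive symptoms compared with the control group". The control group is thus the comparator for the whole list. No time point is named.
- **Analysis.** In Statistical analyses the neuropsychological scores at baseline, three and nine months "will be modeled using the linear mixed model for repeated measurements", and the quantities to be reported are "Differences in the estimated means of the changes at three and nine months from baseline between the intervention and control groups". The section then adds: "Secondary outcomes (cerebral functioning, the GDS and GAI scores, and telomere lengths) will be analyzed similar to the primary outcomes".
- **Schedule.** Under Nine months (study end): "Blood samples (3 mL) will be collected at three time-points for those in the AT and MRA arms". Of controls the same section says: "For the control group, it will be done twice, at baseline and at nine months". The neuroimaging section agrees: "The only difference is the control group will not have blood samples taken at three months". Table 1 lists a three-month blood sample for the active arms; Table 2 lists none for controls.

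**The concern.** The outcome list and the analysis section together call for a three-month telomere difference between each active arm and control, but the schedule provides no control data for it. This is not a matter of missing detail: the article fixes an outcome time, a type of contrast and a sampling schedule that do not fit together.

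The risk lies in what gets reported. The Background mentions preliminary telomere changes after three months of weekly sessions in the team's previous trial, so a three-month result will attract interest here. Without three-month controls, what an active arm offers against no treatment is its own before-after change. Listed as an efficacy outcome of a randomised trial, that change could be taken for a controlled effect.

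**Working it through.** **The plan's own figure.** The article gives no sample size for telomere length. The one it gives, for neuropsychological scores at three months, reproduces. With a 90% interval of full width 1 SD, n = 2 × (1.645 / 0.5)² = 21.64, rounded up to 22 per group. Allowing for 25% drop-out, 22 / 0.75 = 29.33, rounded up to 30 per group, 90 in total. Nothing here disputes it.

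**Telomere data by arm and visit** (Tables 1 and 2 and the text around them):

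| Arm | Baseline | 3 months | 9 months |
|---|---|---|---|
| Art therapy (AT) | yes | yes | yes |
| Music reminiscence (MRA) | yes | yes | yes |
| Control | yes | **no** | yes |

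Eight of nine cells are filled. The control cell at three months is empty by design: 0 of 30 planned controls.

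**Estimability.** Write μ(arm, month) for the cell mean. The planned contrast at month t is

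Δ(t) = [μ(active, t) − μ(active, 0)] − [μ(control, t) − μ(control, 0)].

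In a cell-means model with visit as a category, the design matrix built from the filled cells has rank 8. A contrast is estimable only if adding its row leaves the rank at 8.

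| Contrast in change | 3 months | 9 months |
|---|---|---|
| AT − control | not estimable | estimable |
| MRA − control | not estimable | estimable |
| AT − MRA | estimable | estimable |

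So two of the four contrasts with control are lost, both at three months.

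**Why the mixed model does not help.** It can accommodate values missing for some members of an arm because others in that arm identify the mean. Here μ(control, 3) has no observations at all.

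**What an assumption would do.** Let D be the mean control change from baseline to nine months. If control change is taken as linear in time, the three-month value is (3/9) × D = D/3. If controls are taken not to have changed by three months, it is 0. The two resulting effects differ by D/3, and no three-month control data exist to choose between them. The article states neither assumption.

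**Imaging, for consistency.** Scans are scheduled at baseline and three months in every arm, so six of nine cells are filled. All three-month contrasts are estimable and no nine-month contrast is. Outcomes lists cerebral functioning at three months only, which matches the schedule.

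**The case against.** The best reply has four parts.

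1. *The three-month contrast is inferred.* No single sentence says that three-month telomere change will be compared with control, and an increase could mean change within an arm. This is fair as to wording. But the analysis section names telomere length, offers no other analysis for it, and the hypothesis is stated against control. The inference is the natural one.
2. *The unequal sampling is disclosed, and the analysis plan can deal with it.* It is disclosed three times, and nobody is misled about which samples exist. General wording elsewhere, under Three months and under Risks and safety monitoring, does not exempt controls from the three-month draw, but the control-specific statements settle the matter. An analysis plan, however, cannot supply unmeasured values. It can only drop the contrast or add an assumption, and the outcome statement should match that choice.
3. *The hypothesis survives.* This stands. A reader might infer that the telomere hypothesis can no longer be tested. The documents do not support that: the hypothesis names no time point, and all three arms are sampled at baseline and nine months.
4. *Imaging is not affected in the same way.* This also stands. A reader might infer that a nine-month imaging contrast is promised as well. It arises only if the sentence on analysing secondary outcomes similarly is taken to carry over every time point. Outcomes limits imaging to three months, so this is loose wording and not a second failed contrast.

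**Conclusion.** The point holds for the three-month telomere comparison with control: two of four contrasts, with 0 of 30 planned controls contributing a value. It rests on two readings: that the analysis section's contrast applies to telomere length at both listed times, and that visit is modelled as a category. Treating time as linear would produce a number, but the control part of it would come from the assumption and not from data.

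The grade is should-fix. Telomere length is a secondary outcome in a study that calls itself a pilot. Its nine-month contrasts with control, the three-month comparison of the two active arms, the neuropsychological and mood outcomes, three-month imaging and the sample size are all untouched. A more serious grade would require the outcome as a whole to be lost, and it is not.

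**What to change.** - **Outcomes and Statistical analyses:** state that telomere length is compared with control at nine months only.
- **Three-month telomere data:** report them as within-arm change in the two active arms and as an exploratory comparison of AT with MRA, with no efficacy claim against control. That comparison is randomised and fully sampled, and Aims of study already treats AT versus MRA as exploratory, so it should be kept.
- **Minor consistency edit in Statistical analyses:** say that cerebral functioning is compared at three months only, as Outcomes already does.

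The cost is wording only: no change to sample size, visits or sampling. The trial gives up only a three-month claim against control that its data could not support. Keeping that claim would instead mean adding a control draw. That changes the design in the neuroimaging section, the blood-sampling text and Table 2, in a trial whose recruitment began in June 2016 and which is due to end in April 2017.
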